**10. Efficacy, Health Outcome/Quality of Life Measures, and Safety Evaluations, and Appropriateness of**

**Measurements**

Study procedures and their timing (including tolerance limits for timing) are summarized in the Study Schedule (Protocol Attachment LYDZ(b).1).

**10.1. Efficacy Measures**

***10.1.1. Primary Efficacy Measure***

**10.1.1.1. Conners’ Adult ADHD Rating Scale-Investigator Rated: Screening**

**Version (CAARS-Inv:SV)**

The primary efficacy measure for this study is the CAARS-Inv: SV. This scale will be administered at every visit.

The CAARS-Inv: SV is a 30-item scale containing 3 subscales: the Inattention subscale

(items 1, 9, 13, 14, 19, 21, 26, 29, and 30), the Hyperactivity-Impulsivity subscale (items

2, 4, 6, 8, 16, 18, 22, 25, and 27), and the ADHD Index (items 3, 5, 7, 10, 11, 12, 15, 17,

20, 23, 24, and 28) (Conners et al. 1999). The 18-item total ADHD symptom score is the sum of the Inattention and Hyperactivity-Impulsivity subscales. Each individual item is scored on a 0 to 3 scale (0 = not at all, never; 1 = just a little, once in a while; 2 = Pretty much, often; 3 = very much, very frequently). The rating scale will assess the symptom severity over the past week. The scale will be administered and scored by qualified personnel at the investigative site. The Inattention subscale, Hyperactivity/Impulsivity subscale, ADHD Index subscale, and the 18-item total ADHD symptom score will be computed. The scale is scored by a qualified rater based on an interview with the patient.

***10.1.2. Secondary Efficacy Measures***

The following secondary efficacy measures will be collected at the times shown in

Attachment LYDZ(b).1 (Study Schedule).

**10.1.2.1. Adult ADHD Quality of Life (AAQOL-29)**

The AAQOL-29 is a patient-reported outcome measure used to examine the disease- specific functional impairments and quality of life for adults with ADHD. The domains included in the AAQOL are life productivity, psychological health, quality of relationships, and life outlook. Consistent with the majority of existing quality of life measures, higher scores on the AAQOL-29 indicate better functioning. A longer version of this scale, which includes 80 items, was used in two atomoxetine studies: B4Z-MC- LYBV and B4Z-US-LYCU (Brod et al. 2005).

**10.1.2.2. Clinical Global Impression—ADHD-Severity (CGI-ADHD-S)**

The CGI-ADHD-S is a single-item clinician rating of the clinician’s assessment of the patient’s severity of the ADHD symptoms in relation to the clinician’s total experience with ADHD patients (Guy 1976; NIMH 1976).Severity is rated on a 7-point scale

(1 = normal, not at all ill; 7 = among the most extremely ill patients).

**10.1.2.3. Conners’ Adult Attention-Deficit/Hyperactivity Disorder Rating**

**Scale–Self Report**−**Screening Version-Administered (CAARS-S:SV*)*** The CAARS-S:SV is the same scale as the CAARS-Inv: SV, but it is completed by the patient. The individual items, subscales, and scoring will be the same as described for the CAARS-Inv: SV.

**10.1.2.4. Patient Global Impression-Improvement (PGI-I)**

The PGI-I is a 7-point scale modeled after the CGI on which patients rate any change in their overall status that they had experienced since beginning the study drug. The score on this scale ranges from 1 (very much improved) to 7 (very much worse).

**10.1.2.5. Montgomery Asberg Depression Rating Scale (MADRS)**

The MADRS (Montgomery et al. 1979) is a widely used rating scale for severity of depressive mood symptoms and is administered by the investigator. The scale consists of

10 items, each rated on a scale from 0 to 6. The MADRS total score is the sum of the 10 items and the score ranges from 0 to 60. Higher scores denote more severe depressive symptoms.

Item 10 (Suicidal Thoughts) is specifically evaluated to determine suicidal risk. For this study, a **baseline score of 3 or greater** on Item 10 (Suicidal Thought) of the MADRS scale is an automatic exclusion from the trial.

A **post-baseline** score of **2 or greater** on Item 10 (Suicidal Thought) of the MADRS scale at Visit 4, 6, and 9 will require the administration of the Columbia Suicide-Severity Rating Scale.

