**Clinical Protocol Synopsis: Study B4Z-US-LYDZ(b)**

| **Name of Investigational Product:** Atomoxetine hydrochloride (LY139603) | |
| --- | --- |
| **Title of Study:** A Double-Blind Study of Atomoxetine Hydrochloride versus Placebo for the Treatment of ADHD in Young Adults with an Assessment of Associated Functional Outcomes | |
| **Number of Planned Patients/Subjects:**  Entered: 550  Enrolled/Randomized: 446  Completed: 117 | **Phase of Development:** IV |
| **Length of Study:** 19 Months  Planned first patient visit: 16 August 2007 Planned last patient visit: 10 March 2009 | |
| **Objectives:**  **Primary Objective:** The primary objective of this study is to compare the efficacy of atomoxetine at  40-100 mg/day dosed BID and placebo on the reduction of ADHD symptoms after 12 weeks of double- blind treatment as measured by the mean change in the Conners’ Adult ADHD Rating Scale- Investigator Rated: Screening Version (CAARS-Inv:SV) total ADHD symptom score in young adults ages 18 to 30 who meet criteria for ADHD as defined by DSM-IV-TR.  **Secondary Objectives:** The secondary objectives of the study are:  • To assess the efficacy of atomoxetine therapy compared with placebo on the total score of the  Adult ADHD Quality of Life -29 (AAQOL-29).  • To assess the efficacy of atomoxetine therapy compared with placebo on the subscales of the AAQOL-29 in the following order: Relationship; Life Productivity; Psychological Health; and Life Outlook.  • To test the hypothesis that atomoxetine improves symptoms of ADHD compared to placebo after  12 weeks of treatment on the mean change from baseline to endpoint as measured by:  -Clinical Global Impression-ADHD-Severity (CGI-ADHD-S)  -CAARS Self Report (CAARS-S:SV)  -Patient Global Impression – Improvement (PGI-I)  • Montgomery Asberg Depression Rating Scale (MADRS): To assess the effect of atomoxetine in treating symptoms of depression in adults with ADHD as measured by the mean change in the total score after 12 weeks of treatment.  • Beck Anxiety Inventory (BAI): To assess the effect of atomoxetine in treating symptoms of anxiety in adults with ADHD as measured by the mean change in the total score after 12 weeks of treatment.  • To assess the correlation between the improvements on the AAQOL-29 Total Score with symptom reduction as measured by improvement on the CAARS-Inv:SV total ADHD symptom score. | |

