A **post-baseline** spontaneous report of suicidal thoughts or behavior at any visit OR a score of **2 or greater** on Item 10 (Suicidal Thought) of the MADRS scale at Visit 4, 6, and 9 will require the administration of the Columbia Suicide-Severity Rating Scale.

If in the PI’s clinical judgment, the PI determines the patient to *not* be at serious suicide risk (using Columbia scale as a tool), the patient may continue in the study.

If in the PI clinical judgment, the PI determines the patient to be at serious suicidal risk, the risk should be addressed immediately using the PI’s best clinical judgment. Further,

a. serious suicidal risk is exclusionary and the patient must be discontinued, and

b. the site must contact and inform the sponsor of the event within 24 hours by contacting the Clinical Research Associate (CRA) who will then contact the Lilly study physician.

[21] Are currently using alcohol, drugs of abuse, or any prescribed or over-the- counter medication in a manner which the investigator considers indicative of DSM-IV-TR™ criteria for substance abuse or dependence.

If the urine drug screen is positive for any substance, the investigator should discontinue the patient *only* if the substance is being used in a manner indicative of DSM-IV-TR™ criteria for substance abuse or dependence OR

if the substance is on the excluded medication list (Protocol Attachment

LYDZ(b).3) and the patient cannot or will not discontinue the medication.

[22] Are taking any psychotropic medication on a regular basis, including health- food supplements that the investigator feels have central nervous system activity (for example, St. John’s Wort, melatonin, etc.).

[23] Have a current diagnosis of uncontrolled hyper- or hypothyroidism. Patients with an initial abnormal TSH screen should be evaluated with additional

thyroid tests through a local lab to determine eligibility for the study or the need for treatment prior to re-screening and participation in the study. **Note:** Patients previously diagnosed with hyperthyroidism or hypothyroidism that have been treated on a stable dose of thyroid supplement for at least the past

3 months immediately prior to Visit 1, have medically appropriate TSH

concentrations, and are clinically euthyroid are allowed.

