**8.3. Discontinuations**

***8.3.1. Discontinuation of Patients***

The criteria for enrollment must be followed explicitly. If a patient who does not meet enrollment criteria is inadvertently enrolled, that patient should be discontinued from the study, and Lilly or its designee must be contacted.

In addition, patients will be discontinued from the study drug and from the study in the following circumstances:

• Enrollment in any other clinical trial involving an off-label use of an investigational drug or device or enrollment in any other type of medical research judged not to be scientifically or medically compatible with this study.

• If Exclusion Criterion [11-32] is observed, or develops, after entry or enrollment. In this case, the patient will be discontinued from the study at the next visit or sooner in the event of a safety exclusion criterion.

• The investigator decides that the patient should be withdrawn. If this decision is made because of a serious adverse event or a clinically significant laboratory value, the study drug is to be discontinued and appropriate measures are to be taken. Lilly or its designee is to be alerted immediately. Refer to Section 10.3, Safety Evaluations.

• The patient or attending physician requests that the patient be withdrawn from the study.

• The patient, for any reason, requires treatment with another therapeutic agent that has been demonstrated to be effective for treatment of the study indication. In this case, discontinuation from the study occurs prior to

introduction of the new agent.

• The investigator or Lilly, for any reason, stops the study or stops the patient's participation in the study.

Patients who discontinue the study early will have end-of-study procedures performed as shown in the Study Schedule (Protocol Attachment LYDZ(b).1).

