***9.1.2. Study Period III***

All eligible patients who complete the double-blind Study Period II will have the option

of participating in a 12-week open-label extension period. In Study Period III, study drug

(atomoxetine) will be dispensed to all patients.

Dosing of atomoxetine during the open-label period will commence the morning immediately following the last dose of blinded medication. Dosing may be once daily or twice-daily administration. It is strongly recommended to take the study medication with food.

The starting dose of atomoxetine will be initiated at 7 days of 40 mg/day followed by 7 days of 80 mg/day for those dosed once daily. For those patients prescribed BID dosing in the open-label period, 18 mg capsules were chosen for the lowest starting dose as 20 mg capsules are not available in the marketed form of atomoxetine.

After the initial titration period, the dose may be titrated freely (that is, the dose may be increased or decreased at any time) between 36 mg/day and 100 mg/day during the remainder of Study Period III depending on the patient’s clinical response.

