***10.1.2.5.1. Columbia Suicide-Severity Rating Scale:***

The Columbia Suicide-Severity Rating Scale is a physician administered scale to evaluate suicidal intent and plan and is used in this study as a *required tool* to evaluate serious suicidal risk. The scale evaluates 3 categories: suicidal behavior, suicidal ideation, and intensity of ideation. For the purposes of this study, it will be required as part of an algorithm should a patient score 2 or greater on Item 10 of the MADRS scale at Visit 4,

6, or 9 OR should a patient spontaneously report suicidal thoughts, plans, or behavior. This tool will assist the investigator to determine if the patient is at serious suicidal risk.

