**Protocol Attachment LYDZ(b).1.**

**Study Schedule**

**Study Schedule, Protocol B4Z-US-LYDZ(b)**

| **Study Period** | **I** | | **II** | | | | **III** | | |
| --- | --- | --- | --- | --- | --- | --- | --- | --- | --- |
| **Visit** | **1** | **2** | **3** | **4** | **5** | **6**  **SUM IIa** | **7** | **8** | **9**  **SUM IIIa** |
| **Weeks Until Next Visit:** | **1** | **2** | **3** | **3** | **4** | **2** | **5** | **5** | **N/A** |
| **Interval Between Visits and**  **Target ( )** | **5-28 (7)** | **10-18 (14)** | **17-25 (21)** | **17-25 (21)** | **25-31 (28)** | **10-18 (14)** | **28-38 (35)** | **28-38 (35)** | **-** |
| Informed consentb | X |  |  |  |  |  |  |  |  |
| Patient number assigned | X |  |  |  |  |  |  |  |  |
| Inclusion/exclusion criteria  (including PHQ-9) | X |  |  |  |  |  |  |  |  |
| Presenting/preexisting conditionsc | X |  |  |  |  |  |  |  |  |
| Medical/psychiatric history | X |  |  |  |  |  |  |  |  |
| Physical Exam | X |  |  |  |  |  |  |  |  |
| Height | X |  |  |  |  |  |  |  |  |
| Weight | X | X | X | X | X | X | X | X | X |
| Vital signs | X | X | X | X | X | X | X | X | X |
| Demographics | X |  |  |  |  |  |  |  |  |
| Social Demographics | X |  |  |  |  |  |  |  |  |
| Previous drug therapy- ADHD | X |  |  |  |  |  |  |  |  |
| Previous drug therapy- all other  CNS Therapies | X |  |  |  |  |  |  |  |  |
| Concomitant medications | X | X | X | X | X | X | X | X | X |
| Adverse events | X | X | X | X | X | X | X | X | X |
| Dispense drug |  | X | X | X | X | X | X | X |  |
| Study drug compliance |  |  | X | X | X | X | X | X | X |
| **Investigator-Administered Scales:** | | | | | | | | | |
| ASRS (prior to v1 via web) | X |  |  |  |  |  |  |  |  |
| SCID-RV | X |  |  |  |  |  |  |  |  |
| ACDS v1.2 | X |  |  |  |  |  |  |  |  |
| CAARS-Inv-SV | X | X | X | X | X | X | X | X | X |
| CGI-ADHD-S | X | X | X | X | X | X | X | X | X |
| MADRS | X |  |  | X |  | X |  |  | X |
| **Patient-Rated Scales: d** | | | | | | | | | |
| AAQOL-29 |  | X | X | X | X | X |  |  | X |
| CAARS-S:SV | X | X | X | X | X | X | X | X | X |
| PGI-I |  |  | X | X | X | X |  |  | X |
| Habits Timeline Followback: (Alcohol, Nicotine, Caffeine, Marijuana, and Drug) |  | X | X | X | X | X |  |  | X |
| Fagerstrom Test for Nicotine  Dependence |  | X |  | X |  | X |  |  | X |
| SASS |  | X |  | X |  | X |  |  |  |
| Driving Behavior Survey - Self  Report |  | X |  | X |  | X |  |  |  |

|  |  | |  | | | |  | | |

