| --- | --- | --- | --- | --- | --- | --- | --- | --- | --- |
| **Study Period** | **I** | | **II** | | | | **III** | | |
| **Visit** | **1** | **2** | **3** | **4** | **5** | **6**  **SUM IIa** | **7** | **8** | **9**  **SUM IIIa** |
| Driving Behavior Survey - Other  Report |  | X |  | X |  | X |  |  |  |
| BRIEF-A |  | X |  | X |  | X |  |  |  |
| Epworth Sleepiness Scale |  | X | X | X | X | X |  |  | X |
| Beck Anxiety Inventory |  | X |  | X |  | X |  |  | X |
| **Laboratory Measures:** | | | | | | | | | |
| Chemistry e | X |  |  |  |  | X |  |  | X |
| Hematology e | X |  |  |  |  | X |  |  | X |
| Cotinine e | X |  |  |  |  | X |  |  | X |
| TSH e | X |  |  |  |  |  |  |  |  |
| Urinalysis e | X |  |  |  |  | X |  |  | X |
| ECG | X |  |  |  |  | X |  |  | X |
| CYP2D6 f |  |  |  |  |  |  |  |  |  |
| Blood Alcohol Screen e | X |  |  |  |  |  |  |  |  |
| Urine Drug Screen e, g | X |  |  |  |  |  |  |  |  |
| Pregnancy test e, h | X |  |  |  |  |  |  |  |  |

Abbreviations: X = required at this visit; AAQOL-29 = Adult ADHD Quality of Life Scale 29-item; ACDS = Adult ADHD Clinician Diagnostic Scale version 1.2; ASRS = Adult ADHD Symptom Rating Scale; BRIEF-A = Behavior Rating Inventory of Executive Function-Adult Version-Self; CAARS- Inv:SV = Conners’ Adult ADHD Rating Scale-Investigator Rated: Screening Version; CAARS-S:SV = Conners’ Adult ADHD Rating Scale-Self-Report: Screening Version; CGI-ADHD-S = Clinical Global Impressions –ADHD and Severity; MADRS = Montgomery-Asberg Depression Rating Scale; PGI-I = Patient Global Impression – Improvement; PHQ-9 = Patient Health Questionnaire; SASS = Social Adaptation Self-Evaluation Scale ; SCID-RV = Structured Clinical Interview for DSM-IV Axis Disorders-Research Version.

a Study Period II and Study Period III will have summarization packets for the completion or early

discontinuation from each Study Period.

b A waiver with privacy statement and informed consent (ICD) is obtained prior to patient completing the ASRS and inclusion/exclusion questions via website. An additional online ICD is obtained by the investigator site prior to or at Visit 1 if patient is eligible to proceed to the randomized clinical trial. **Consent must be obtained prior to beginning any medication washout required for the sole purpose of entering this study- even if the washout is commenced prior to Visit 1.**

c Presenting/preexisting conditions does not include symptoms of ADHD.

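### No scheduled suicidality rating between Visit 6 and Visit 9: for 84 target days of open-label atomoxetine, MADRS Item 10 cannot inform a decision to stop drug

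*Protocol*

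**What the plan says.** The protocol gives two post-baseline routes to the Columbia Suicide-Severity Rating Scale.

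- **Score-based.** Under Section 10.1.2.5, an Item 10 score of 2 or more "of the MADRS scale at Visit 4, 6, and 9 will require the administration of the Columbia Suicide-Severity Rating Scale". Section 8.2, criterion [20], and Section 10.1.2.5.1 name the same three visits.
- **Unscheduled.** Criterion [20] also counts a "spontaneous report of suicidal thoughts or behavior at any visit", and Section 10.1.2.5.1 repeats this: "OR should a patient spontaneously report suicidal thoughts, plans, or behavior".

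If the investigator then judges the patient to be at serious suicidal risk, criterion [20] requires discontinuation. For exclusion criteria that emerge after entry, Section 8.3.1 adds that "the patient will be discontinued from the study at the next visit or sooner in the event of a safety exclusion criterion".

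In Attachment LYDZ(b).1 the MADRS row is marked at Visits 1, 4, 6 and 9 and is empty at Visits 7 and 8. The PHQ-9 is listed at Visit 1 only. The dispensing row reads "Dispense drug | | X | X | X | X | X | X | X", that is, Visits 2 to 8 and not Visit 9. Footnote a says that "Study Period II and Study Period III will have summarization packets for the completion or early" discontinuation of each period, so the summary-visit assessments are also done when a patient leaves early.

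Section 9.1.2 starts open-label atomoxetine the morning after the last blinded dose. Patients dosed once daily take 40 mg/day for 7 days and then 80 mg/day for 7 days. "After the initial titration period, the dose may be titrated freely" between 36 and 100 mg/day.

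**The concern.** The protocol singles out Item 10 as its measure of suicidal risk, calls the Columbia scale a required tool, and makes serious suicidal risk a mandatory reason to stop. In Study Period III the scheduled rating behind that chain is taken only before open-label drug starts and when treatment is ending.

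Every patient is then on atomoxetine. Those from the placebo arm are taking it for the first time and pass through titration and free dosing with no scheduled question about suicidal thoughts. A patient who has such thoughts but does not volunteer them may go unnoticed until Visit 9. A positive score there still leads to the Columbia scale and to clinical care, but it cannot change dosing or prompt stopping. Nor can the scheduled scores place the onset within the 84 days.

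Entry rules do not remove the issue. Baseline exclusion is an Item 10 score of 3 or more, so a patient scoring 2 may enrol. A patient who scores 2 or more at Visit 6 but is judged not to be at serious risk may continue. Having completed Study Period II, that patient is eligible for the extension, with no scheduled repeat rating until the end.

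**Working it through.** **Inputs (Attachment LYDZ(b).1, target and window in days)**

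| Interval | Target | Window |
|---|---|---|
| Visit 2 to 3 | 14 | 10–18 |
| Visit 3 to 4 | 21 | 17–25 |
| Visit 4 to 5 | 21 | 17–25 |
| Visit 5 to 6 | 28 | 25–31 |
| Visit 6 to 7 | 14 | 10–18 |
| Visit 7 to 8 | 35 | 28–38 |
| Visit 8 to 9 | 35 | 28–38 |

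Section 12.1 gives 220 patients per arm, 440 in total, and 68% completing 12 weeks.

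**1. The plan's own figure.** Study Period III is stated as 12 weeks: 12 × 7 = 84 days. The targets agree: 14 + 35 + 35 = 84.

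**2. Gap without a scheduled Item 10 rating, Visit 6 to Visit 9.** The target is 84 days. The windows give 10 + 28 + 28 = 66 to 18 + 38 + 38 = 94 days.

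**3. Free-dosing part.** From Visit 7 to Visit 9 the target is 35 + 35 = 70 days (56 to 76). Section 9.1.2 ties free dosing to the end of titration, not to Visit 7. With a fixed 14-day titration, as stated for once-daily dosing, the target is 84 − 14 = 70 days and the range is 66 − 14 = 52 to 94 − 14 = 80 days.

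**4. Comparison with the double-blind period.** Visit 2 to Visit 4 is 14 + 21 = 35 days (27 to 43). Visit 4 to Visit 6 is 21 + 28 = 49 days (42 to 56). Both periods have a 12-week target; the blinded one has a mid-period rating and the open-label one has none.

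**5. Patients concerned.**
- Former placebo patients: 220 × 0.68 = 149.6, at most about 150. This assumes 68% completion in the placebo arm and that every completer takes up the optional extension.
- All patients: 440 × 0.68 = 299.2, at most about 299 on the same assumptions.
- The synopsis has "Completed: 117" without saying which period is meant. If it means patients finishing Study Period III, split equally by arm, then 117 / 2 = 58.5, or about 58 former placebo patients. Neither part of that reading is stated in the protocol.

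**6. With Item 10 added in Study Period III.**

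| Ratings added at | First open-label rating, day | Longest gap, days |
|---|---|---|
| None (as planned) | 84 (66–94) | 84 (66–94) |
| Visit 7 only | 14 (10–18) | 70 (56–76) |
| Visit 8 only | 49 (38–56) | 49 (38–56) |
| Visits 7 and 8 | 14 (10–18) | 35 (28–38) |

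Extra ratings: 2 × 299 = 598 at most.

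**The case against.** The strongest reply is that nothing here is misstated. The schedule and the three sections on Item 10 agree with one another, so this is a design choice. Several safeguards also operate between Visits 6 and 9. A spontaneous report at any visit requires the Columbia scale, adverse events are recorded at Visits 7 and 8, the investigator sees and rates the patient at both visits, and the sponsor's physician monitors safety throughout (Section 10.3.3). Entry excludes patients at serious suicidal risk, major depression within the past year, and any lifetime bipolar disorder or psychosis. Extension patients have completed Study Period II, with Item 10 scheduled at Visits 4 and 6. The drug is approved for adults and the doses follow the label.

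Those safeguards are real, and they keep the point from being critical. They depend, however, on the patient volunteering or the investigator happening to ask. A scheduled item covers the patient who does neither, and the protocol did not rely on spontaneous report alone in Study Period II.

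Three further objections stand in part.

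- **No count of missed cases.** The protocol gives no rate of suicidal ideation on atomoxetine and no sensitivity for Item 10 over ordinary visit contact. The size can be given only in days and patients.
- **The 49 days from Visit 4 to Visit 6.** Section 9.1.1 has active drug started by Visit 4 at the latest, and the dose may rise at Visit 5 without a MADRS. The same argument applies there in weaker form. The difference is that the Visit 6 result is available before a patient goes on to more drug; the Visit 9 result is not.
- **First exposure.** This argument covers former placebo patients only. The total of 299 includes patients already exposed and rated on atomoxetine.

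**Conclusion.** The concern holds as a limited one about the scheduled rating. Between Visit 6 and Visit 9, 84 target days (66 to 94), no scheduled Item 10 score can inform stopping open-label atomoxetine. The early-discontinuation packet does not change this, because it follows the decision to leave. The 84 days are the longest such stretch on study medication, and they include the first exposure of at most about 150 former placebo patients.

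The day counts come straight from the schedule. The patient counts are upper bounds that rest on 68% completion and full uptake of the extension; the lower figure of about 58 rests on an assumed reading of the synopsis. No efficacy analysis, sample size or primary conclusion is affected. The change is worth making because the gap is real and cheap to close, and the remaining routes do not ask the question routinely.

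**What to change.** In Attachment LYDZ(b).1, mark MADRS Item 10 (or the full MADRS) at Visits 7 and 8. In Section 8.2, criterion [20], and Sections 10.1.2.5 and 10.1.2.5.1, extend the list of trigger visits to 4, 6, 7, 8 and 9. Keep the threshold of 2, the spontaneous-report trigger and the investigator's decision rule unchanged. Both visits are wanted, since either one alone leaves a gap of 70 or 49 target days. Study Period II can stay as it is.

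The cost is a schedule and wording amendment. There is no new visit, and because the period is open-label there is no effect on blinding. The investigator already rates CAARS-Inv:SV and CGI-ADHD-S at Visits 7 and 8, so the burden is a few minutes per visit and at most about 598 ratings in all, plus some additional Columbia interviews. The Columbia scale is physician administered. A site led by a psychologist, as Section 13.3.1 allows, would need its physician sub-investigator available at those two visits.
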